## Abstract

**Introduction:**

Society associates palliative care with "death" or "end of life", which cause them fear and anxiety. In Spain, the media worsens the misunderstanding by depicting a wrong picture of palliative care. Educational innovation for university students may serve as an alternative communication strategy. Care and Society is a university course designed by and for students from non-health degrees to help disseminate the palliative care message. The first year of the Teach-Inn Pal project aims to evaluate the effects of the course and to identify areas of improvement.

**Objective:**

To present an evaluation to determine if the course can work as a campaign to refocus the public opinion on palliative care and share the preliminary results of the pilot study.

**Methodology:**

A prospective Participatory Action Research study. University students enrolled in the course (n = 29) are invited to test and redesign the palliative care message. Knowledge and empathy will be measured throughout the learning process. Afterwards, qualitative, thematic, inductive analysis of the course material will be carried out. This study is registered on the ISRCTN Registry under the name “Can a university course help communicate palliative care?” (Registration number: ISRCTN10236642).

**Discussion:**

This study is part of a doctoral thesis. Education is used as a creative outlet, allowing rapid testing of multiple tools to create ambassadors of palliative care that may reframe the public opinion.

**Conclusion:**

The understanding of students about palliative care changed, the overall impression of the experience was positive, and students were also able to explain palliative care to people with little or no experience in the topic. However, to determine if they became ambassadors the results of the mid-term assessment are required.

## 1. Introduction

Palliative care is a worldwide necessity: more than 56.8 million people need specialized care for an incurable disease each year [1]. In response to this reality, palliative care started in 1967, when Cicely Saunders founded the first hospice dedicated to providing an integral support (physical, emotional, social, and spiritual) to terminally ill patients to improve their quality of life [2, 3]. However, at present, the supply of palliative care is still not sufficient to meet the demographic demand [4, 5].

The European Association of Palliative Care (EAPC) suggested a minimum of two specialized palliative care services for every 100.000 inhabitants [6]. And yet, there are few countries that reach this threshold. From the 49 countries analyzed in the EAPC Atlas of Palliative Care in Europe, the only country that met this recommendation was Austria, with 2.2 palliative care specialized services [6]. Yet, the rest of the countries fell short on this requirement: on average, there only were 0.8 specialized services per 100,000 inhabitants [6]. As for the education, palliative care is increasingly being included in the curricula across European Medical and Nursing Schools. However, the percentage of Schools teaching palliative care per country and the way it is taught varies greatly [6]. Only 9 countries report teaching palliative care as a mandatory subject, and very few countries report offering over 20 palliative care teaching hours and mandatory clinical practice [6].

More specifically, in Spain there are 0.6 specialized services per 100,000 inhabitants [6]. And even if more than half of the Medical and Nursing Schools offer subjects related to palliative care, only 48% of the Nursing Schools and 10% of the Medical Schools include these studies as a part of their obligatory curricula [6].

Furthermore, palliative care has a communication problem, as 54 years after its creation the concept is still misunderstood. Palliative care is currently perceived as "death" or "end of life”, and that misconception continues to generate feelings of bereavement, fear, and anxiety in society [7, 8]. In Spain, the media may play an important role in this misunderstanding. An analysis of 600 Spanish newspapers (2009–2014) concluded that information on palliative care does not reflect its true nature, as the narratives used to talk about it are based on ideological and moral content such as the debate of issues like euthanasia [9]. The importance of this study stems from the need to find alternative routes to reach an alienated audience. Society receives a distorted version of the palliative care message and identifying a more direct channel of communication could be a solution.

## 2. State of the art

### 2.1 Educational innovation strategy

Health-related issues are frequent in the public opinion sphere. Therefore, the possibilities offered by communication for the development of a healthier society have been studied for years [10, 11]. Due to its evolution and persuasive capacity, communication has become an essential component of health prevention and health promotion programs to inform and educate citizens [10, 12, 13]. Within the health sector, communication campaigns facilitate social education because they seek to increase the knowledge to encourage new behaviors [10, 12, 14, 15]. And these campaigns have secondary goals, such as bringing attention to an issue to create an agenda [14, 16, 17].

However, the benefits also work the other way around. Educational programs such as Massive Online Open Courses (MOOC), despite not being an explicit communication campaign, have successfully started conversations around several topics and helped clarify issues [18]. MOOCS have also been widely used to disseminate research results beyond the academic sphere [19]. Specifically, the Dying2Learn MOOC demonstrated that the educational ambiance was favorable to increase participants’ comfort to discuss difficult issues such as death, to foster conversations about this topic, and to explore unheard perspectives from people outside the healthcare context [20]. These results can be a foundation for the development of palliative care resources and information context [20]; which, in turn, could be the basis for formal communication campaigns.

On that line, some social studies have focused on finding new ways to overcome the confusion generated around palliative care [21, 22]. The last diagnostic study of the EnPositive-PAL project conducted with university students all over Spain highlighted that it is positive to involve students when designing a strategy to disseminate the palliative care message [23]. It used the Participatory Action Research method, Design Thinking and adopted a strategy of public engagement in Responsible Research and Innovation with the idea of creating a social intervention to promote a transformative, active, and service-learning approach [23]. The result of this process is Care and Society: a four-module course (Fig 1) aimed to create a meaningful learning experience for Spanish university students from degrees unrelated to the health sector.

**Fig 1 pone.0286343.g001:**
[figure not shown]
Course structure diagram. You can find further information on the Modules on section 2.3.

### 2.2 Why university students from degrees unrelated to the health sector

In a health communication campaign, a desirable outcome is for the target audience to become an ambassador of the cause. Ambassadors, otherwise known as influencers, are people that can exert interpersonal influence or help reform the environmental condition that shapes the behaviors of the segment to be changed [24]. Creating ambassadors have two advantages. Firstly, they can customize the message to the needs and values of their peers [24]. Peer to peer communication has been proven to facilitate health messaging, because fellow community members are both trusted and relatable, and able to express information in an understandable and significant way [25]. Secondly, ambassadors are likely to respond to negative behaviors of those they are attempting to influence [24]. This type of engagement provides opportunities for giving instant feedback, having open dialogues, and answering questions immediately [26].

Moreover, as the issue of palliative care in the academic curricula of health-related degrees is already being tackled [27, 28], the aim of this course is to reach students belonging to areas of expertise outside the sector. Considering the two previous advantages, students with different backgrounds and areas of expertise are an ideal group to create ambassadors, as the variety of backgrounds will allow the palliative care message to be disseminated beyond the field of health. The social intervention proposes to reach the students through the Core Curriculum: an initiative designed to offer students from a wide range of degrees an integral education in core areas of study [29, 30]. Aligned with that objective, the Core Curriculum course Care and Society seeks to convey to the university students the value of caring for others within society.

### 2.3 Care and Society course structure

#### 2.3.1 Module I: Transformative learning

In this module, through flipped classes, the students will receive the theory required to face the rest of the course. The students will learn to identify situations of serious illness that involve intense suffering, and to outline a set of actions that help to care for the person suffering. During this segment, the total of students will be divided in three groups to encourage participation and to adapt the class to the necessities of everyone. The groups will switch professors every two weeks, as each professor will oversee the explanation of a set of topics related to one of three categories: cancer, dementia, and neurodegenerative illnesses.

#### 2.3.2 Module II: Active learning

Through a self-learning circuit inspired on an Escape Room dynamic, students will be the protagonists in building their own knowledge. By the end of the module, the students will be able to understand what the process of assisting, caring and alleviating suffering is like. The total of students will be divided in groups of six to facilitate and encourage the interaction of students with the environment.

#### 2.3.3 Module III: Service learning

Students will participate individually in community service activities, allowing them to link what they have learned in modules I and II with the local context. By the end of the module, the student will have developed their personal and professional competencies, and will be able to evaluate, implement, and recommend good practices when caring for people.

#### 2.3.4 Module IV: Multiplier learning

All students will attend a four-hour seminar titled “An introduction to rhetoric” that will give them some resources to improve their ability to express themselves and construct valid arguments on a topic. By the end of the module, the students will be able to plan a persuasive speech according to the basics of rhetoric. The seminar will be led by a teacher specialized in communication and will be taught to all students together.

## 3. Method

This pilot study, of the three-year multicenter project Teach-Inn Pal, is part of a doctoral thesis. The project started on November 2021 and will continue until September 2024 in Spain. The pilot study took place on the second semester of the academic course 2021–2022, starting on January 2022 (Fig 2). However, enrollment to the course took place five months before, in August of 2022, when the university course registration period was open.

**Fig 2 pone.0286343.g002:**
[figure not shown]
SPIRIT schedule of enrollment, interventions, and assessments. The SPIRIT schedule is copyrighted by the SPIRIT Group and is reproduced with permission.

### 3.1 Objective

Using an interdisciplinary approach, Care and Society focuses on promoting the knowledge of palliative care and increasing the empathy of students on issues related to accompanying and caring for people suffering from a serious illness. The objective of this protocol is to present the possible evaluation of Care and Society as public health communication strategy. This proposal stems from the recognition that education is inherent to communication, and therefore aims to evaluate the communicative worth of innovative education to promote a positive message of palliative care.

This research aims to address two questions:

Is educational innovation a suitable solution to the communication necessities of palliative care?Can students help amplify the palliative care message?

### 3.2 Research design

It is a prospective study with a participatory action research framework, using multiple methods for data collection such as application of scales, satisfaction questionnaires, focus groups and direct observation. Participatory action research is composed of cyclical steps of planning, action, observation, and results, making participants evolve from the beginning [31, 32]. This allows us to receive feedback and incorporate it to improve both the course and the assessment techniques along the process before their implementation in other universities. Consequently, this is considered a pilot study, deeming the course Care and Society the prototype of the social intervention. We understand that evaluations related to the changes in attitudes and behaviors cannot be based on immediate results. Therefore, it is intended that this evaluation will be conducted over 3 years, giving us the opportunity to repeat the intervention and see its results in medium-term.

### 3.3 Participants

During the pilot, the course will be offered as an elective class to a maximum of 30 students in a Spanish university. All students who desire to participate in the course can enroll as long as they: (1) are in their second or subsequent years of university, (2) are from the Schools of Economics and Business, Architecture, Education and Psychology, and (3) their fields are not related to health.

### 3.4 Moments of evaluation

The evaluation will assess the capacity of the course to turn students into ambassadors that can change the framework of the discussion in society. We understand as ambassadors the students who demonstrate: (1) an adequate degree of understanding of the concept of palliative care, (2) a positive attitude towards the social problem, (3) the ability to communicate the message of palliative care and (4) to retain the knowledge five months after taking the course. The overall assessment of the course will focus on four moments of evaluation (Fig 3).

**Fig 3 pone.0286343.g003:**
[figure not shown]
Diagram of moments of evaluation. You can find further information on the Moments of Evaluation on the following sections.

#### 3.4.1 Moment 1: Initial assessment

In Moment 1, one week before the beginning of the course, students will receive an email inviting them to participate in the study. The invitation will have three links: one to the initial Palliative Care Knowledge Questionnaire (PCKQ), another to a Cognitive and Affective Empathy Test (TECA), and the last to a consent form for recontact. The initial PCKQ is meant to examine participants previous knowledge on palliative care. If any student shows a formidable knowledge on the topic, they will not be excluded from the study. Their performance will simply be recorded, and any improvement will be taken into consideration.

#### 3.4.2 Moment 2: Learning assessment

Following the end of Module I, students will receive links to the PCKQ and TECA of Moment 2. Furthermore, to evaluate Module II for teaching purposes, a ten-minute debriefing will be recorded at the end of the Escape Room. With their written consent, transcripts of this recording will be used to help analyze the data.

#### 3.4.3 Moment 3: Final assessment

The final two classes in the course contemplate a seminar where students will learn the basics of Rhetoric. They will write a speech, applying the knowledge of palliative care acquired during the course and the resources given throughout the seminar. The speeches will be sent to and graded by the professor, who will forward them to the research team to be analyzed accordingly. The teacher will then proceed to select the five best speeches for a Message Transmission Experiment. For this experiment, five selected students will deliver their speech in front of first-year students not enrolled or related in any way to the course. Following the speeches, the first-year students will fill out a questionnaire to assess their understanding of palliative care after the experience.

Additionally, prior to the last day of class, students will turn in a written reflection regarding the Module III experience. This material will also be analyzed for the research with the prior written consent of the students. After the class is over, students will receive the link to answer the last PCKQ and TECA. Participants will also receive a link to provide feedback on the course through a satisfaction and commitment questionnaire that includes an open question and a learning commitment regarding an attitude change: "After what you have learned in this course, what do you intend to change in your attitude in the coming months to enhance the palliative care message?".

Lastly, all the students and teachers of Care and Society will be invited to participate in a focus group to evaluate the overall experience in this course. The first five students who respond to this request will be selected. The purpose of this focus group is not to evaluate the knowledge of the participants, but to discuss the strengths and weaknesses of the methodology, the content and other aspects of the course. The focus groups will later be transcribed, and thematic content analysis of the material will be carried out.

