## 4. Preliminary results

The first edition of Care and Society took place from January to May 2022. The course had 29 students enrolled. For the preliminary results, we compared the PCKQ answers of the participants throughout the course. We also assessed the results of the Message Transmission Experiment, and we obtained an initial overview of the recurring themes of the focus group.

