### 4.2 Message Transmission Experiment

During the last class of the course, five students were selected to read out loud their speech in front of their classmates and two guests. The guests were two first-year students not enrolled in the course, who have previously display little or no knowledge regarding palliative care in an assignment delivered for another university course. After hearing all the speeches, they were asked to define palliative care (S2 File). One of them defined palliative care as "a medical treatment intended for patients with a terminal illness with the aim of reducing their suffering as much as possible". The other one wrote that palliative care "is a special care that focuses on people who do not have the possibility of being cured of their illness. They try to support, both focused on the disease and psychological consequences, to the patient and the family".

Two lessons can be drawn from this experience. The first one is that the students were able to learn the basics of rhetoric from the four-hour seminar. The speeches written for the experiment were well structured and clearly expressed the concepts that the students had learnt during the course. The second one is that the speeches showed signs of being effective in conveying the concepts learnt throughout the course to the guests. The guests, who presumably knew little or nothing about palliative care prior to the experience, provided an acceptable definition of palliative care after hearing the speeches. Thus, the students of the course showed their ability to communicate and retransmit the palliative care message to their peers.

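### The Message Transmission Experiment uses teacher-selected speeches and questions recipients only afterwards, so it cannot carry the general statements about the students in section 4.2 and the abstract

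*Protocol article*

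**What the plan says.** The plan for this component is in section 3.4.3 of the protocol article.

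- **Speeches.** Enrolled students write a speech. "The speeches will be sent to and graded by the professor, who will forward them to the research team to be analyzed accordingly".
- **Speakers.** "The teacher will then proceed to select the five best speeches for a Message Transmission Experiment".
- **Recipients.** They are first-year students with no link to the course. "Following the speeches, the first-year students will fill out a questionnaire to assess their understanding of palliative care after the experience". No questionnaire before the speeches, and no recipients without speeches, are described.

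Section 4.2 reports how it was run. "The guests were two first-year students not enrolled in the course". An assignment for a different course had suggested that they knew little about palliative care, and the article describes them as people "who presumably knew little or nothing about palliative care prior to the experience". They were asked for a definition once, after all the speeches.

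The conclusions differ in strength:

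- Section 4.2 ends by saying that "the students of the course showed their ability to communicate and retransmit the palliative care message to their peers".
- The abstract says that "students were also able to explain palliative care to people with little or no experience in the topic".
- Section 7 restricts the statement to some students, words it as an appearance, and asks for better assessment of what recipients knew beforehand.

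The limitations in section 6 mention neither the choice of the best speeches nor the after-only measurement.

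**The concern.** Two separate features of the design limit what can be concluded.

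1. **Selection of speakers.** They are chosen on the quality of their speech, which is close to the ability under evaluation. What they achieve does not describe the class.
2. **Measurement of recipients.** The study's own instrument is applied only after the speeches. How much the guests' answers changed is not observed. Because both guests heard all five speeches, no answer can be tied to one speaker.

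This matters because the ability to communicate the message is the third of the four ambassador criteria in section 3.4, and the second research question in section 3.1 asks whether students can amplify it. The experiment is the only described component that puts questions to recipients. Under the present procedure, acceptable definitions could be obtained even if most of the class could not transmit the message, or if the guests could already have given such a definition.

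**Working it through.** The article gives no sample size, error rate or target for this component, so there is no stated figure to reproduce. The sums below only show how little the data can carry.

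**Inputs from the article**
- Class size 29 (section 4: "The course had 29 students enrolled"); 25 students agreed to take part (section 4.1).
- Five speakers, the best by the teacher's judgement (section 3.4.3). Section 4.2 says only that five were selected; I take it that the planned rule was followed.
- Two recipients (section 4.2), both judged by the authors to have given an acceptable definition.

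**Step 1: from five speakers to the class.** The selected share is 5/29 = 17% (5/25 = 20% on the participants). Suppose all five can transmit the message. The other 24 were not tested, so the share of the class with that ability could lie anywhere from 5/29 = 17% to 29/29 = 100%.

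**Step 2: size of the selection effect (assumptions).** Assume roughly normal grades and a speech from all 29. The expected mean of the top five of 29 standard normal values, from 200,000 simulated classes, is 1.43 SD above the class mean (1.35 SD for 25). Multiply by an assumed correlation between grade and transmission ability:

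| Assumed correlation | Excess of the selected five, class of 29 |
|---|---|
| 0.3 | 0.3 × 1.43 = 0.43 SD |
| 0.5 | 0.5 × 1.43 = 0.71 SD |
| 0.7 | 0.7 × 1.43 = 1.00 SD |

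The article gives no correlation, so this is a range and not an estimate.

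**Step 3: precision with two recipients.** For 2 of 2, the exact two-sided 95% lower limit p solves p² = 0.025, so p = √0.025 = 0.158. The interval is 16% to 100%. It treats the guests as independent, although they heard the same speeches in one session.

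**Step 4: what no transmission would produce.** If a proportion p₀ of such guests could give an acceptable definition beforehand, 2 of 2 occurs with probability p₀² when the speeches add nothing:

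| Assumed p₀ | p₀² |
|---|---|
| 30% | 9% |
| 50% | 25% |
| 70% | 49% |

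The informal evidence in section 4.2 points towards a low p₀, but p₀ was not measured with the study questionnaire.

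**Step 5: the conclusions side by side.** Section 7 (some students, appearance only, prior knowledge to be assessed better) fits the selection of speakers and acknowledges the weak baseline. The closing sentence of section 4.2 and the clause in the abstract mention neither the selection nor the presumed baseline, and neither is limited to some of the students.

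**The case against.** The other side has real points.

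- **Other evidence is planned.** A reader might infer that this is the only test of the third criterion and of the second research question. The article does not support that. The speeches go to the research team for analysis (section 3.4.3), and the five-month interviews ask whether students have passed the message on (section 3.4.4). What stands is narrower: those sources are text analysis and self-report, and only the experiment questions recipients.
- **A baseline of a kind existed.** A reader might infer that nothing was known about the guests beforehand. In fact the assignment showed their knowledge of this very topic. It was informal, not made with the study instrument, and the authors themselves treat it as a presumption.
- **The authors hedge.** Section 4.2 also says that the speeches gave signs of being effective, the abstract leaves ambassador status to the mid-term results, and section 7 is cautious. This stands, and it is why the remedy for the pilot is to align two sentences.
- **Best speakers can be legitimate.** In a participatory prototype, showing that transmission is possible is a fair aim, provided that the conclusion is confined to the selected speakers.
- **A pre-questionnaire may prime recipients.** Section 6 raises a related worry about repeated questionnaires. The cost is real but small.
- **One guest's definition.** It still centres on terminal illness, as the Moment 1 answers in section 4.1 did, and a reader might count it as a failure. The article sets no such scoring rule, and similar wording appears in Moment 2 answers that the authors treat as a shift in perspective. It shows only that a single answer given afterwards cannot be read as change.

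**Conclusion.** The point holds in a limited form. Five teacher-selected speeches, heard by two guests without a study pre-measure, cannot support general statements about the ability of the students of the course. Section 4.2 and the abstract make such statements; section 7 largely does not.

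The main conclusion rests on the text alone: selection on speech quality, measurement only afterwards, and two recipients who heard every speech. The 17% to 100% range for the class assumes only that all five speakers succeeded. The 16% lower limit assumes independent guests. The 0.4 to 1.0 SD selection effect and the 9% to 49% chance of two acceptable answers without transmission rest on assumed values and are illustrations.

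The article does not support going further and saying that the experiment is worthless or that the students cannot transmit the message. This is one qualitative component of a pilot that section 3.2 says is meant to improve the assessment techniques before use at other universities. The issue should be fixed, but it is not critical to the whole evaluation.

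**What to change.** **For later editions**
1. Give recipients the same questionnaire, including the request for a definition, before and after the speeches, and report the paired change. The cost is one extra completion of an existing form. Priming can be reduced by giving the first one some days earlier.
2. Choose one of two options and state it. Either draw the speakers at random from consenting students, which allows a statement about the class but may give less polished speeches, or keep the teacher's best five and limit the conclusion to selected speakers, which costs nothing.

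**For the pilot**

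Bring the closing sentence of section 4.2 and the matching clause in the abstract into line with section 7. State that the result comes from five teacher-selected speeches and two guests with no study pre-measure, and that it allows no inference on the ability of the class. Add the speaker selection and the after-only measurement to section 6. This is a change of wording only.
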